#### Plans to promote participant retention and complete follow-up {18b}

A regular telephone follow-up will be performed every 3 months in the participating centers.

#### Data management {19}

Data will be entered into online encrypted database and a separate Excel form from the CRC staff. Researchers must have an authorized account to access the database.

#### Confidentiality {27}

All personal information about potential and enrolled participants will be safely maintained in order to protect confidentiality before, during, and after the trial.

#### Plans for collection, laboratory evaluation, and storage of biological specimens for genetic or molecular analysis in this trial/future use {33}

No biological specimens were collected as part of this trial.

### Statistical methods

#### Statistical methods for primary and secondary outcomes {20a}

Statistical analyses are performed using SPSS version 20.0 software (SPSS Inc., Chicago, IL, USA). The statistical analysis will be performed in accordance with both the intention-to-treat and the per-protocol principles. Survival will be estimated by Kaplan–Meier methods and analyzed using log-rank test. Continuous variables will be compared using a Student’s *t* test or Wilcoxon rank-sum test as appropriate and represented as the mean ± standard deviation or as median and range. Categorical variables will be compared using Fisher’s exact test or Wilcoxon rank-sum test as appropriate and represented as number of patients and percentage. For the analysis of QoL, parametric or non-parametric statistical methods will be used to assess the results of QLQ-C30 and QLQ-OES18 from pretreatment to 12 months, depending on the data distribution.

#### Interim analyses {21b}

An interim analysis will be performed after 80 patients have been included. The safety parameter will be analyzed by the statistical analysts. In case the stop rule is reached, the trial will be stopped immediately in all participating centers. Patients who have already been included will not undergo any further research-related tests. These patients will be scheduled for surgical resection according to the standard protocol for esophageal cancer.

Stop rule: The safety parameter is defined as peri-treatment mortality.

If the 30-day mortality after esophagectomy or the mortality in the duration of dCRT reaches 5%, then this trial will be stopped.

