### Trial design {8}

This study is a multicenter, randomized, open-label, phase III trial. All participants will be allocated to the two intervention groups at 1:1 ratio. The flow chart is illustrated in Fig. 1.

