## Methods: Participants, interventions, and outcomes

### Study setting {9}

Patients with cN0-pT1b ESCC after ESD will receive two concurrent salvage treatments. The intervention randomly assigned with either esophagectomy or dCRT will start at about 3 weeks after ESD, followed by a 60-month follow-up period. To achieve the primary endpoint, 176 patients will be recruited from three high-volume centers (>100 cases of esophagectomies) in China (Shanghai Chest Hospital, Zhongshan Hospital, and Changhai Hospital).

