### Sample size {14}

According to previous studies, the 5-year OS of patients with pT1b ESCC who underwent esophagectomy was 70 ~ 80% [23] whereas the rate was about 90% in patients who received ER plus chemoradiation [16]. We assumed that the 5-year OS rates were 75% in the esophagectomy group and 90% in the dCRT group. The proportion dropping out of the study is considered to be 5%. Therefore, a sample size of 88 patients in each group is required at a significance level of 5% and a power of 80%.

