### Recruitment {15}

All patients with cN0-pT1b ESCC diagnosed after ESD treatment are potential candidates in this trial. The endoscopists will register all of these patients and notify the clinical research coordinator (CRC) of this trial, and the CRC will contact and tell potential candidates about this trial. After screening for the eligible criteria, the CRC will set up a meeting with potential candidates or their authorized surrogates and [name] in the outpatient clinic. [name] will explain the details of this trial to them and obtain their signatures.

The three institutions which are participating in this trial are high-volume medical centers with esophagectomy and ESD treatment. According to our estimation of the duration of recruitment, 80 patients will be recruited per year.

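### The only scheduled use of the 5% peri-treatment mortality rule is one look triggered by inclusion of 80 patients, not by completion of the period the rule measures; none is scheduled for the other 96

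*Protocol article*

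**What the plan says.** Interim analyses {21b} describes one analysis. Its timing is "An interim analysis will be performed after 80 patients have been included". Its content is the safety parameter, defined as peri-treatment mortality: "The safety parameter will be analyzed by the statistical analysts". The rule reads: "If the 30-day mortality after esophagectomy or the mortality in the duration of dCRT reaches 5%, then this trial will be stopped". The section names no later look and no data cut-off. It does not require the 80 patients to have passed 30 days after surgery or finished dCRT, and it gives no denominator for the percentage.

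Other sections supply the timing. Recruitment {15}: "According to our estimation of the duration of recruitment, 80 patients will be recruited per year". Trial design {8}: "All participants will be allocated to the two intervention groups at 1:1 ratio". Study setting {9} says that treatment "will start at about 3 weeks after ESD, followed by a 60-month follow-up period". The dCRT section prescribes 28 fractions, five per week.

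Three sections describe wider oversight. Composition of the data monitoring committee {21a} makes safety monitoring the committee's main task. Adverse event reporting and harms {22} has all adverse events recorded. Frequency and plans for auditing trial conduct {23} sets three-monthly audits and committee meetings throughout the trial. None of the three refers to the 5% rule or to a mortality threshold.

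**The concern.** A peri-treatment mortality rule protects patients only if it is applied to patients whose peri-treatment period has been observed, and for as long as patients are being treated. Here the trigger counts entries into the trial, while the parameter needs a treatment period that the most recent entrants have not finished and may not have started. More than half of the planned sample enters after the only look at which the protocol says the rule is assessed. If an arm with unacceptable mortality passes that look by chance, the protocol does not say that the rule will be applied to it again.

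The missing denominator also matters, because the boundary sits on a step. With 40 patients in an arm, 2 deaths are 2/40 = 5.0% and stop the trial; with 41, 2/41 = 4.9% and do not. Whether included or fully observed patients are counted can therefore change the decision.

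**Working it through.** The plan states no operating characteristics for the rule, so there is no figure of its own to reproduce on this point. The steps below use its stated inputs.

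**Inputs from the protocol article.** Total 2 × 88 = 176 patients; look at 80; accrual 80 per year; 1:1 allocation; windows of 30 days after surgery or the length of dCRT; 28 fractions at 5 per week.

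**Assumptions.** The lag from randomization to treatment is not stated and is taken as 0 to 21 days. Accrual is steady. For step 2, data are cut on the day of the 80th inclusion.

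**1. Window length.** 28 fractions at 5 per week are 5 weeks plus 3 fractions, about 38 calendar days (up to 40, depending on the starting weekday). Averaged over 1:1 arms: (30 + 38)/2 = 34 days, or (30 + 40)/2 = 35 days.

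**2. Patients still in their window at the 80th inclusion.** Accrual is 80/365.25 = 0.219 per day.
- No lag: 0.219 × 34 to 35 = 7.4 to 7.7 patients.
- 21-day lag: 0.219 × 55 to 56 = 12.0 to 12.3 patients.

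So about 7 to 12 of the 80 are incompletely observed, leaving roughly 68 to 73 complete, or about 34 to 36 per arm. The count scales with accrual: about 4 to 6 at 40 per year and 9 to 15 at 100 per year.

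**3. Patients entering after the look.** 176 − 80 = 96; 96/176 = 54.5%.

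**4. Chance that an arm passes the look.** With 34, 36 or 40 patients, 5% is reached at 2 deaths, so the arm passes with 0 or 1: P(pass) = (1 − p)^n + n·p·(1 − p)^(n−1). The true rates p are illustrative; 8% is not in the document.

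| Complete per arm | p = 5% | p = 8% |
|---|---|---|
| 40 (all windows complete) | 40% | 16% |
| 36 | 46% | 21% |
| 34 | 49% | 23% |

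Most of the pass probability comes from the small number of patients at a single look. Incomplete windows add about 6 to 9 percentage points at 5% and 5 to 7 at 8%. That is an upper bound, since a death already seen in a patient still in the window could be counted.

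**5. What follows a pass.** About 96/2 = 48 patients per arm remain. Expected peri-treatment deaths among them are 48 × 0.05 = 2.4 at 5% and 48 × 0.08 = 3.8 at 8%.

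**6. Effect of continuing the same rule.** Start at 40 completed patients in an arm, then re-apply the 5% rule as each further patient completes, up to 88. The stopping boundary is 2 deaths at 40, 3 at 41–60, 4 at 61–80 and 5 at 81–88. An exact binomial recursion gives the per-arm probability of stopping:

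| True mortality | One look at 40 | Continued to 88 |
|---|---|---|
| 2% | 19% | 23% |
| 8% | 84% | 94% |

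For either arm to stop the trial when both have 2% mortality: 1 − (1 − 0.19)² = 34% with one look, and 1 − (1 − 0.23)² = 41% with continuation (40% from unrounded values).

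**The case against.** The strongest reply is that the rule sentence carries no time limit. Nothing in it confines the 5% to the first 80 patients, deaths are recorded throughout, and the data monitoring committee has safety as its main task. A reader might infer from the single look that the remaining patients are never checked and are left unprotected. The document does not support that: it is an inference from silence, and deaths could well be noticed and acted on. What remains is narrower. No application of the 5% rule is scheduled outside that look, and the sections on oversight do not connect to it.

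Second, the text says the look comes after 80 inclusions and fixes no cut-off. Waiting some weeks for windows to close would be consistent with it. This stands, so the 7 to 12 patients are conditional on a cut at the 80th inclusion. The upper end is also unlikely: treatment starts about 3 weeks after ESD, and randomization needs the ESD pathology and consent first.

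Third, a reader might add the in-window patients to the 96 and say that about 60% of the trial escapes the rule. That overstates it. In-window patients are partly observed at the look; the share wholly after it is 54.5%.

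Fourth, a cut-off and denominator are details that a full protocol, analysis plan or committee charter may supply, and their absence from an article would not by itself be a finding. But the article does fix the trigger, the parameter and a single look, and the trigger as fixed does not match the parameter.

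**Conclusion.** The point holds in limited form. The only documented application of the 5% mortality rule is one look triggered by inclusion rather than by completed peri-treatment windows, and 96 of 176 patients (54.5%) enter after it with no scheduled application. The 54.5% rests only on the protocol's own counts. The 7 to 12 incompletely observed patients rest on steady accrual at 80 per year, a 0 to 21 day lag and a cut at the 80th inclusion.

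The larger weakness is the single look, not the trigger: with every window complete, an arm at 8% true mortality still passes with probability 16%, and one at 5% with probability 40%. It would be wrong to attribute those figures to the inclusion trigger. The point does not judge the 5% threshold or show that safety is unmonitored. It should be corrected because the rule is the protocol's only explicit mortality stopping criterion.

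**What to change.** Amend Interim analyses {21b} in three places:

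1. Take the look when the 80th patient has completed the peri-treatment window (30 days after esophagectomy, or the end of dCRT).
2. Use as each arm's denominator only patients whose window is complete.
3. State that the same rule continues to be applied, by arm, to cumulative peri-treatment deaths after the look until the last patient's window closes. Say who applies it, and report the overall stopping probabilities over a range of true mortality rates.

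The threshold itself is left to the sponsor.

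The cost is protocol wording and a running count of deaths that are already recorded as adverse events. The look moves later by roughly one window plus the lag to treatment. The statistical downside is a slightly higher chance of a false stop, from about 19% to 23% per arm at 2% true mortality, against a rise in detection from 84% to 94% per arm at 8%. If the sponsor finds the false-stop chance too high, the reported stopping probabilities will show it before the rule is used.

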## Introduction

### Background and rationale {6a}

Esophageal cancer is the seventh most common malignant tumor and ranks sixth in tumor-related mortality worldwide [1]. In terms of the histological subtypes, adenocarcinoma is frequently observed in Europe and the United States whereas squamous cell carcinoma is the predominant form in China [2].

Tumor invasion of the submucosa (T1b) is a watershed in the treatment of esophageal cancer from endoscopy to esophagectomy. Esophagectomy with extended lymph node dissection is recommend as the primary treatment for pT1b esophageal squamous cell carcinoma (ESCC) because of the high incidence of lymph node metastasis [3, 4]. Previous studies showed that patients with pT1b ESCC after esophagectomy had a favorable 5-year survival rate, which was about 70 ~ 73.6% [5, 6]. Although 30 ~ 50% of these patients have a risk of lymph node metastasis, more than half of them are presented with local superficial lesions [7]. In addition, esophagectomy is associated with a higher morbidity and mortality rate as well as decreased quality of life (QoL) [8]. Therefore, preserving the esophagus has always been the ultimate goal of treatment for low-risk submucosal esophageal cancer.

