### Interventions

#### Explanation for the choice of comparators {6b}

The comparator of this trial is esophagectomy. The rate of lymph node metastasis in patients with pathological T1b ESCC was high (20 ~ 50%). According to the current National Comprehensive Cancer Network (NCCN) guidelines of esophageal and gastric cancer, esophagectomy is the primary treatment option for pathological T1b ESCC. The 5-year OS of patients with pT1b ESCC who underwent esophagectomy was 70 ~ 80%. So the comparator we choose for this trial is esophagectomy with lymphadenectomy.

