##### Definitive chemoradiotherapy (dCRT)

Radiotherapy will be delivered with photons (6–10 MV) in daily fractions on 5 days per week. Intensity-modulated radiation therapy based on a computed tomography (CT) simulation planning system with 5-mm-thick scan slices throughout the entire neck and thorax and upper abdomen is required.

Target volumes need to be carefully defined.

Gross tumor volume (GTV): The GTV should include the positive margin according to the pathology after ESD.

Clinical target volume (CTV): The CTV is defined as tumor bed and elective lymph node regions. For the proximal third of the esophagus, consider treatment of para-esophageal lymph nodes, bilateral supraclavicular lymph nodes, and mediastinum lymph nodes. For the middle third of the esophagus, consider treatment of para-esophageal lymph nodes. For the distal third of the esophagus, consider para-esophageal, lesser curvature, splenic nodes, and celiac axis nodal regions.

Planning target volume (PTV): The PTV includes PTV-G and PTV-C. Owing to set-up deviation and organ movement, PTV-G is defined as a further 6- to 10-mm expansion to the GTV in all directions and PTV-C is defined as a further 6- to 10-mm expansion to the CTV. The prescribed dose of PTV-G is 6020 cGy (215 cGy/d), PTV-C is 5040 cGy (180 cGy/d), both in 28 fractions.

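### The stop rule has two arm-specific mortality triggers but one action, resection of all included patients, which does not fit those who have completed dCRT and is questionable for untreated patients after a surgical-mortality stop

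*Protocol article*

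**What the plan says.** The protocol article, Interim analyses {21b}, plans one safety look after 80 inclusions and sets two alternative triggers, one per arm: "If the 30-day mortality after esophagectomy or the mortality in the duration of dCRT reaches 5%, then this trial will be stopped". If either is met, all centers stop at once.

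The section then says what happens to patients already in the trial. First, "Patients who have already been included will not undergo any further research-related tests". Next, "These patients will be scheduled for surgical resection according to the standard protocol for esophageal cancer". The second sentence refers back to the first, so its subject is every included patient. No other section narrows it by trigger, by arm or by how far treatment has gone.

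Two other statements bear on how to read it. Explanation for the choice of comparators {6b} says, citing guidelines, that "esophagectomy is the primary treatment option for pathological T1b ESCC". Background and rationale {6a} says that "preserving the esophagus has always been the ultimate goal of treatment for low-risk submucosal esophageal cancer".

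**The concern.** The two triggers mean opposite things. Deaths during dCRT are a reason to move patients who have not yet had it to surgery. Deaths after esophagectomy are a reason to pause before sending more patients to surgery. A single action cannot suit both.

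The action also ignores treatment status. By the time 80 patients are in, most will have finished their allocated treatment. For a patient who has completed definitive dCRT, the sentence schedules an esophagectomy because the trial stopped, with no recurrence or residual disease required.

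What is at stake is the care of included patients once a safety rule has fired. Sites would either have to follow an instruction that does not fit most of the patients it names, or depart from the protocol at that moment.

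**Working it through.** The plan gives no figure on this point to reproduce. The check sets trigger against treatment status, then counts the patients in each state.

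**Trigger by status**

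| Status at the stop | Stop for dCRT deaths | Stop for esophagectomy deaths |
|---|---|---|
| Already resected | No effect | No effect |
| dCRT completed | Adds an operation with no stated clinical reason | Same, and it is the operation that triggered the stop |
| On dCRT | Possibly coherent | Sent to the operation that triggered the stop |
| Untreated | Coherent | Sent to the operation that triggered the stop; arguable as standard care |

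**Inputs**

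- Interim look at 80 inclusions (Interim analyses {21b}) with 1:1 allocation (Trial design {8}): 40 per arm.
- Accrual (Recruitment {15}): "According to our estimation of the duration of recruitment, 80 patients will be recruited per year".
- Time to treatment (Study setting {9}): "either esophagectomy or dCRT will start at about 3 weeks after ESD". Inclusion needs the ESD pathology, so it follows ESD, and 3 weeks is roughly the longest lag from inclusion to treatment. I use 0 to 3 weeks.
- dCRT duration (Definitive chemoradiotherapy): 28 fractions, given "in daily fractions on 5 days per week", so 28/5 = 5.6 weeks. The last chemotherapy day, day 32, falls within that.
- Assumptions: even accrual, exactly 40 per arm, the look at the 80th inclusion, and no deaths or drop-outs.

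**Counts** (patients in a state = accrual rate × time in that state)

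- Accrual: 80/52 = 1.54 per week, or 0.77 per arm per week.
- Untreated at a 3-week lag: 0.77 × 3 = 2.3 per arm, 4.6 in all.
- On dCRT: 0.77 × 5.6 = 4.3.
- Finished dCRT: 40 − 2.3 − 4.3 = 33.4.
- Already resected: 40 − 2.3 = 37.7.
- Check: 4.6 + 4.3 + 33.4 + 37.7 = 80.0.

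At a lag of 0 weeks, nobody is untreated, 40 − 4.3 = 35.7 have finished dCRT and 40 have been resected. So the range is 0 to 5 untreated and 33 to 36 finished with dCRT.

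The sentence is therefore coherent for at most about 4.6 + 4.3 = 8.9 of 80 patients, counting those on dCRT, and only after a dCRT-mortality stop. A later look would leave more patients already treated.

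**Could a trigger be met?** With 40 per arm, one death is 1/40 = 2.5% and two are 2/40 = 5%, so two deaths suffice. The probability of at least two is 1 − (1−p)^40 − 40p(1−p)^39. For an assumed true mortality of 1%, 2% or 3% this gives 0.06, 0.19 or 0.34 in that arm. The documents give no peri-treatment mortality, so these rates only illustrate that a stop is possible in either arm.

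**The case against.** The best defence is that the sentence means a return to standard care. Scheduling describes treatment still to come, and the sentence appeals to the usual protocol for esophageal cancer. It is empty for the roughly 38 patients already resected, so the authors probably had untreated patients in mind. The comparator section names esophagectomy as the primary option, and dCRT is the treatment under test. Two deaths in 40 have an exact 95% interval of about 0.6% to 17%, which does not show resection to be worse than the alternative.

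Much of this stands for untreated patients. A reader might infer that sending them to surgery after a surgical-mortality stop is plainly wrong. The documents do not support that: it is an arguable default, and about half of those patients (2.3 of 4.6) were allocated to surgery anyway. What remains open to criticism is that it is automatic, with no review of the finding that stopped the trial.

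The defence does not reach patients who have finished dCRT. Nothing in the article presents esophagectomy after completed dCRT, without recurrence, as standard care, yet the sentence includes these patients. The esophagus-preserving statement in the background adds only modest support. It concerns low-risk disease, and the same section recommends esophagectomy for pT1b tumors.

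It can also be said that clinicians would not operate on such patients. That is likely, but it is a reason to correct the instruction. Nor does the condensed form of an article excuse it, because the action is stated, not left out.

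**Conclusion.** The point holds as a defect in a stated rule. The clearest part is the patients who have completed dCRT: about 33 of 80 at the interim (33 to 36 for lags of 3 down to 0 weeks), under either trigger. The weaker part is the automatic resection of about 0 to 5 untreated patients after a surgical-mortality stop. The counts rest on even accrual, 40 per arm and the protocol's own timing.

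Three stronger readings are not supported:

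- A reader might infer that the rule misdirects all of the roughly 71 of 80 patients who have completed treatment. About 38 of these have been resected and are unaffected.
- A reader might infer that patients would not be told of the safety finding. The article's silence on that is not evidence, since such detail commonly sits in the full protocol and consent material.
- A reader might infer that the trial's results are compromised. The defect acts only if the trial stops. Randomization, type I error, power, sample size and the primary analysis are untouched.

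Severity is minor to moderate.

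**What to change.** Replace the resection sentence with text that sets the action by trigger and treatment status, for example:

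> If deaths during dCRT triggered the stop, patients who have not begun their allocated treatment will be referred for esophagectomy as standard care. If deaths after esophagectomy triggered it, treatment of those patients, including whether to proceed to resection, will be decided individually after review of the safety finding. Patients who are receiving or have completed dCRT will not be referred for resection solely because the trial has stopped; they will be managed on clinical grounds.

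The cost is a short protocol amendment, best made before the 80-patient look. Sample size, endpoints, analysis and data collection do not change. The amendment leaves open whether the 60-month follow-up continues after a stop. The follow-up sections do not address a stopped trial, and the interim section ends research-related tests, so that would be a separate decision for the sponsor.

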#### Who will be blinded {17a}

Because of the different interventions in the two groups, the thoracic surgeons or radiologists will not be blinded to group allocation. Statistical analysts will be blind to the procedure and the results of randomization, group allocation, and intervention.

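### The 5% mortality stop rule holds two unlike death windows to one threshold and turns a crude percentage at about 40 per arm into a mandatory stop

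*Protocol article*

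**What the plan says.** The rule is in the protocol article under Interim analyses {21b}. Its timing is given as: "An interim analysis will be performed after 80 patients have been included". The quantity monitored is named first, "The safety parameter is defined as peri-treatment mortality", and is then made operational by the rule itself: "If the 30-day mortality after esophagectomy or the mortality in the duration of dCRT reaches 5%, then this trial will be stopped". The consequence is not discretionary: "In case the stop rule is reached, the trial will be stopped immediately in all participating centers". The section gives no confidence bound, tolerated rate or error probability.

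The calculation is assigned as follows: "The safety parameter will be analyzed by the statistical analysts". Under Who will be blinded {17a}, the protocol says of the same people: "Statistical analysts will be blind to the procedure and the results of randomization, group allocation, and intervention".

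Trial design {8} gives the arm sizes at the look: "All participants will be allocated to the two intervention groups at 1:1 ratio". Sequence generation {16a} mentions computer-generated random numbers and no blocking. The section on definitive chemoradiotherapy sets 28 fractions on 5 days a week.

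**The concern.** Two features of the rule pull in different directions.

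First, one threshold is applied to two different quantities. The surgical window, "30-day mortality after esophagectomy", lies entirely after the procedure. The dCRT window closes when treatment ends. A death at a given interval after the operation counts towards stopping, while a death at the same interval after the last fraction does not. For dCRT, the definition therefore does not deliver what the term peri-treatment mortality promises.

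Second, the trigger is an observed percentage in a small arm, and the consequence is immediate and mandatory. At about 40 patients per arm, one death moves the observed rate by 2.5 percentage points. A trial whose true mortality is below 5% in both arms can be ended by chance, and an arm whose true rate is 5% can pass. The protocol does not say how often either would happen, so nobody can tell whether the rule is as cautious as its authors meant it to be.

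**Working it through.** **Inputs from the protocol.** 80 patients at the look and a 5% threshold in either arm (Interim analyses {21b}); 1:1 allocation (Trial design {8}); 28 fractions at 5 per week (definitive chemoradiotherapy section).

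**Assumption.** The protocol gives no expected peri-treatment mortality. True rates of 1% to 5% are assumed below, with 10% added as a clearly high rate.

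**The plan's own figure.** The 5% is stated without derivation or operating characteristics, so there is nothing to reproduce. What can be computed is how the rule behaves.

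**Step 1: windows.** 28/5 = 5.6 weeks, that is five full weeks plus three days, or about 38 days. The dCRT window is thus about 38 days, with none after treatment. The surgical window is 30 days, all after the procedure.

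**Step 2: deaths needed.** The trigger count in an arm of n is the smallest whole number not below 0.05 × n.

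| Arm size | Deaths needed | Observed rate at trigger |
|---|---|---|
| 36 | 2 | 2/36 = 5.6% |
| 40 | 2 | 2/40 = 5.0% |
| 41 | 3 | 3/41 = 7.3% (2/41 = 4.9% does not reach 5%) |
| 44 | 3 | 3/44 = 6.8% |

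The exact (Clopper-Pearson) 95% interval for 2/40 is 0.6% to 16.9%.

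**Step 3: chance that one arm of 40 triggers.** P(at least 2 of 40) = 1 − (1−p)^40 − 40p(1−p)^39. At p = 2%, this is 1 − 0.446 − 0.364 = 0.190.

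| True mortality | P(at least 2 of 40) |
|---|---|
| 1% | 6.1% |
| 2% | 19.0% |
| 3% | 33.8% |
| 5% | 60.1% |
| 10% | 92.0% |

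An arm of 40 truly at 5% therefore escapes with probability 1 − 0.601 = 0.399, about 40%.

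**Step 4: chance that either arm triggers at exactly 40/40.** P(stop) = 1 − (1−a)(1−b), where a and b are the single-arm probabilities.

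- 2% surgery, 1% dCRT: 1 − (1 − 0.190)(1 − 0.061) = 0.24
- 3% surgery, 1% dCRT: 1 − (1 − 0.338)(1 − 0.061) = 0.38

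**Step 5: allowing for unequal arms.** Without blocking, the surgical arm has k of the 80 patients with probability C(80,k)/2^80. An exact 40/40 split has probability 8.9%; in every other split one arm exceeds 40 and needs at least three deaths. The stop probability is recomputed for each k, with the trigger count from Step 2 applied to arms of k and 80 − k, and averaged with these weights.

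| True mortality, surgery / dCRT | Exactly 40/40 | Averaged over unrestricted 1:1 |
|---|---|---|
| 2% / 1% | 24% | 15% |
| 3% / 1% | 38% | 26% |

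One extra patient changes the rule materially: at a true 2%, an arm of 40 triggers 19.0% of the time and an arm of 41 triggers 4.9% of the time.

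**The case against.** The strongest reply is that a cautious single-look mortality rule is a legitimate choice: it catches a true 10% in an arm of 40 about 92% of the time. That stands as a defence of having a strict rule. It does not explain the unlike windows, and it does not excuse leaving the error rates unstated when the stop is mandatory. Nor can the point be left to an SAP, because the article itself fixes the threshold, the windows, the timing and the consequence.

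Several stronger readings are tempting, and the document does not support them.

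- *Two deaths end the trial.* This is true only if the affected arm has 40 patients or fewer. At 41 to 44 it takes three, and blocking is not stated, so the 40/40 figures are upper-end.
- *Deaths soon after dCRT go unseen.* They do not. Adverse event reporting and harms {22} records all adverse events during the study, the DMC section {21a} makes safety monitoring the committee's major task, and the auditing section {23} has the monitoring committee reviewing conduct throughout. Such deaths are missing only from the automatic trigger.
- *The dCRT window is shorter.* In days it is longer, about 38 against 30. The fault is the absence of post-treatment time.
- *Blinded analysts cannot run the rule.* The threshold is the same in both arms, so coded groups and a death flag prepared by trial staff would suffice. The two sections fit awkwardly and should be reconciled, but the rule is workable.
- *The last of the 80 will be analysed before finishing treatment.* The protocol ties the look to inclusion and states no data cut-off. That leaves the denominator open; it does not show that the analysis would be premature.

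**Conclusion.** The point holds in two parts. The mismatch of windows is plain on the text and needs no assumption: early post-dCRT deaths lie outside the stop rule while early postoperative deaths lie inside it, under one 5% threshold.

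The behaviour of the threshold depends on assumed mortality and on arm sizes. With both true rates below 5% (2%/1% or 3%/1%), the chance of a mandatory stop lies between about 15% and 38%, the lower figure in each pair applying if randomisation is unrestricted and the higher if the arms are exactly equal. These figures take all 80 patients as evaluable and the arms as independent. In the other direction, an arm of 40 truly at 5% is missed about 40% of the time. This should be corrected in the protocol, but it does not mean that safety monitoring in the trial is absent.

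**What to change.** In Interim analyses {21b}:

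1. Reconcile the two windows so that both arms count all-cause deaths over a comparable period that includes time after treatment. The length is for the sponsor and the DMC to set and justify.
2. Evaluate the rule in patients who have completed that window, and state the denominator.
3. Keep 5% as the reference, but let reaching it automatically pause recruitment and trigger review by the existing DMC in place of automatic termination. Give the DMC the arm-level counts, the exact interval and the rule's error rates at stated true mortality rates.
4. Reconcile this section with Who will be blinded {17a} on who sees deaths by arm: the DMC, or analysts working with coded groups.

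A window that adds post-treatment time counts more deaths, so the 5% trigger would fire at least as often as now. That is why review should replace automatic termination.

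The cost is an amendment to the protocol and DMC wording; the committee already exists and no additional patients are needed. The downside is that termination would no longer be automatic and would need a DMC decision.
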